**Methods/Design:**

We designed a cluster randomized trial to assess the efficacy of an SMS intervention and a peer-navigation intervention to improve retention in care and treatment, timely linkage to care and treatment, medication adherence, and prevention behaviors in South Africa. Eighteen primary and community healthcare clinics in Rustenburg and Moses Kotane Sub-districts in the North West Province were randomized to one of three conditions: SMS intervention (n = 7), peer navigation intervention (n = 7), or standard of care (n = 4). Approximately 42 participants are being recruited at each clinic, which will result in a target of 750 participants. Eligible participants include patients accessing HIV testing or care in a study clinic, recently diagnosed with HIV, aged 18 years or older, and with access to a cellular telephone where they are willing to receive automated SMS with HIV-related messaging. Data collection includes extraction of visit information from clinical files and participant surveys at baseline, 6 months, and 12 months. Intent-to-treat (ITT) analysis will explore differences between randomization arms and the primary outcome of patient retention in care at 12 months following enrollment. We will also explore secondary outcomes including participants’ a) timely linkage to care (within 3 months of HIV diagnosis), b) adherence to treatment based on self-report and clinic’s medication dispensation dates, and c) condom-use behaviors.

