## Methods/Design

### Study design

Using a cluster randomized trial at the level of the clinic, we will evaluate the efficacy of employing two strategies for enhancing linkage to and retention in clinical care, ART adherence, and HIV preventive behaviors. A target of 750 participants will be enrolled across 18 clinics in the Moses Kotane and Rustenburg Sub-districts, Bojanala Platinum District, South Africa (Fig. 1). Clinics have been randomized to one of three conditions: an SMS intervention arm, a peer navigation (PN) arm that also includes SMS, and a control condition. Clinics have been randomized instead of individuals to avoid contamination of intervention across individuals within clinics and to facilitate cooperation with clinic staff. Participant outcomes will be monitored using both clinical record extraction to document HIV care visits and services and a series of interviewer-administered surveys at enrollment (baseline assessment), 6 months after baseline, and 12 months after baseline.

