### Participant eligibility and recruitment

We will be enrolling 750 participants, with a target of 42 (range = 30-55) participants at each facility. All participants must be diagnosed with HIV within 1 year preceding their enrollment. Participants must also be 18 years or older, have access to a cellular telephone where they are willing to receive automated text messages with HIV-related content, and be willing and able to give informed consent (not under the influence of illicit substances, or seemingly emotionally unstable at the time of recruitment and enrollment). Written informed consent will be obtained from all participants prior to enrollment in the study.

We aim to recruit an equivalent number of men and women and ensure that the sample has substantial representation (minimum of 30 %) of clients who do not yet quality for ART in order to assess the linkage and retention for both clients who initiate ART and those who do not. To accomplish this balance, recruitment will be completed using two strategies. The first strategy includes recruiting clients who present at the clinic for HIV testing and receive a positive diagnosis for the first time, or those who are returning to collect their initial CD4+ test results. Recruitment will be systematic: all of those presenting for an HIV test or for an initial CD4+ test result will be approached by clinic staff about their interest in participating in the study. We initially estimated that between 50 % and 60 % of those recruited during HIV testing would have an ART-qualifying CD4+ cell count at the time of recruitment [38]. Because the national guidelines have recently changed to increase qualifying CD4+ to 500 or less, it is more likely that 70 to 80 % of the individuals newly diagnosed after January 2015 will qualify for ART.

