The second recruitment strategy includes identifying patients from recent entries in the HIV care registers at the clinic sites. This selection will also be systematic: we will enumerate every male and female in the HIV care registers and then systematically select men and women at pre-determined intervals. The selection interval (for example, every fourth woman listed) will differ by clinic depending on the total number of male and female adult registry entries. Because clinic registers are more complete for ART patients than for pre-ART patients (those not yet eligible for ART), we assume that the large majority of patients recruited from the registers (upwards of 90 %) will have qualified for ART. Therefore, we aim to recruit 75 % of our participants through the first strategy and 25 % of participants through the second strategy to ensure that non ART-qualifying participants are included.

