### Measures

Primary and secondary exposure and outcome measures are included in Table 1. Primary exposure for the intent-to-treat analysis is classified as the clinic randomization arm: SMS intervention, PN intervention, and SOC. The primary study outcome is retention in care, which is defined for patients on ART as the proportion of patients who have initiated ART who remain on treatment at 6 and 12 months and for patients who are not yet eligible as the proportion of patients who undergo a repeat CD4 test at 6 months and 12 months after the initial CD4. The secondary outcome of linkage to care is defined as a patient undergoing CD4 staging or being assessed for ART eligibility within 3 months of a positive diagnosis. We will also monitor whether the participants are linked to ART – that is, whether eligible participants receive ART within 3 months of CD4 staging. The secondary outcome of adherence is being assessed in three ways: as a report of taking 90 % of the prescribed medication, as no report or clinical record indicating gaps in treatment of 4 or more days, and collection of the proportion of days covered by medication dispensed. Finally, prevention behavior is defined as the number of unprotected sex acts by HIV partner status. All outcomes will be measured using both clinical record extraction and self-report; these two means of data collection will be compared for accuracy (using clinical record extraction as the gold standard).

**Table 1 Tab1:** Measures, data sources, and data collection schedules for protocol exposures and outcomes

Domain	Instrument/measure	Data source	Data collection schedule
PRIMARY EXPOSURE			
Clinic randomization assignment	Clinic where participant receives care	Intake form	Baseline
SECONDARY EXPOSURE			
Intervention Dosage	Minutes of intervention received	PN participant contact forms and CommConnect system records	Ongoing capture
PRIMARY OUTCOMES			
Retention in HIV care	Patients on or initiating ART who remain on treatment 6 and 12 months later (with documented receipt of treatment)	Intake and Record extraction	Weekly (ART)
		Survey data (self-report)	0, 6, and 12 months
	Patients not ART eligible who have a repeat CD4 test at 6 months and 12 months after initial CD4	Intake and Record extraction	Bi-weekly (pre-ART)
		Survey data (self-report)	0, 6, and 12 months
SECONDARY OUTCOMES			

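### The primary retention outcome is timed from enrolment in the Abstract but from the initial CD4, or from no clear origin, in Measures and Table 1, and at one time point in one place and two in the other

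*Protocol article*

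**What the plan says.** The article describes the timing of the primary outcome in several places.

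- **Abstract (Methods/Design):** "primary outcome of patient retention in care at 12 months following enrollment". The origin is enrolment and there is one time point.
- **Measures, patients not yet eligible for ART:** the proportion who "undergo a repeat CD4 test at 6 months and 12 months after the initial CD4". The origin is the initial CD4 and there are two time points. Table 1 repeats this.
- **Measures, patients on ART:** "the proportion of patients who have initiated ART who remain on treatment at 6 and 12 months". No origin is given.
- **Table 1, patients on ART:** "Patients on or initiating ART who remain on treatment 6 and 12 months later". The event from which the months are counted is not named.
- **Study design:** "surveys at enrollment (baseline assessment), 6 months after baseline, and 12 months after baseline". Table 1 lists these surveys as a data source for both retention rows.
- **Sample size estimation and Discussion:** power is for retention at 12 months, with no origin named.

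Whether the clocks agree depends on who is enrolled. Participant eligibility and recruitment states: "All participants must be diagnosed with HIV within 1 year preceding their enrollment". It also states that "we aim to recruit 75 % of our participants through the first strategy and 25 % of participants through the second strategy". The first strategy takes people who "receive a positive diagnosis for the first time, or those who are returning to collect their initial CD4+ test results"; the second selects patients already in the HIV care registers.

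**The concern.** In a trial that intervenes from enrolment, the primary outcome should be counted from enrolment, or the plan should say why not. Here the Abstract and the outcome definition disagree. For a participant whose initial CD4 came well before enrolment, following Measures as written opens the outcome window before the clinic's intervention could reach that person, while the Abstract opens it on the day of enrolment. The same participant can be retained on one clock and not on the other.

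Three things are at stake. Outcome time before enrolment cannot respond to the intervention, so it pulls the arms together. Exposure at the 12-month point differs between participants for reasons unrelated to the intervention. And if the origin and time point are settled only after data are seen, there is an avoidable choice in the primary endpoint, which also feeds the cost per person retained.

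**Working it through.** **The plan's own figures.** Evaluable sample: 750 × (1 − 0.20) = 600, as stated. With 600/18 = 33.3 per clinic, design effect 1 + (33.3 − 1) × ICC, 50% retention in the reference arm, two-sided 0.05, 80% power and a normal approximation, the detectable difference is 19.4 to 22.2 points for 7 against 4 clinics and 16.6 to 18.9 points for 7 against 7, over ICC 0.0225 to 0.04. The article states 20 to 23 and 17 to 20. The agreement is adequate, and nothing in this point changes those figures.

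**Placing the time points on the enrolment clock.** Let L be the months from the origin (initial CD4 or ART start) to enrolment, negative if the origin comes after enrolment. A point k months after the origin falls at month k − L after enrolment.

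- The initial CD4 and ART start follow diagnosis, and diagnosis is at most 12 months before enrolment, so L ≤ 12.
- 12-month point: 12 − L ≥ 0. It cannot fall before enrolment.
- 6-month point: 6 − L < 0 whenever L > 6. It can fall before enrolment.
- Example, L = 8: the 6-month point is at month −2, and the 12-month point is at month 4 of a 1-year intervention.
- Origin 3 months after enrolment (L = −3): the 12-month point is at month 15, past the last survey and the intervention year.

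**How many participants.** Inputs from Participant eligibility and recruitment: 75% first strategy and 25% registers; upwards of 90% of register recruits qualified for ART; 70 to 80% of new diagnoses qualifying (initially 50 to 60%). Qualifying for ART stands in for being on it.

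- First strategy: 0.75 × 750 = 562.5. Registers: 0.25 × 750 = 187.5.
- Register recruits not qualified for ART: at most 0.10 × 187.5 = 18.75, about 19 (2.5% of 750). These are the register recruits to whom the explicit CD4 origin applies. If 25 to 75% of them had a CD4 older than 6 months (an assumption), 5 to 14 have a 6-month point before enrolment.
- Register recruits qualified for ART: 0.90 × 187.5 = 168.75, about 169 (22.5%). They are exposed only if ART start is the origin; at 25 to 75% with a start more than 6 months earlier (the same assumption), 42 to 127.
- First-strategy recruits qualified for ART: 0.70 to 0.80 × 562.5 = 394 to 450 (52 to 60% of 750), or 0.50 to 0.60 × 562.5 = 281 to 338 under the initial estimate. If ART start is the origin, treatment begins after enrolment within the 3-month linkage window in Measures, and CD4 staging falls close to enrolment, their 12-month point is up to about 3 months after month 12.
- First-strategy recruits not qualified: 562.5 × 0.20 to 0.30 = 112 to 169 (225 to 281 initially). Their initial CD4 is close to enrolment, so the two clocks nearly agree.

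**The case against.** The strongest reply is that only one departure from enrolment is explicit, the CD4 origin, and among register recruits it touches about 19 people at most. For patients already on ART, the Table 1 wording can be read as months after enrolment, which would match the survey schedule. The Abstract, the sample size and the Discussion all point to 12 months. And a condensed article commonly leaves exact windows to the full protocol or analysis plan.

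Much of this stands, and it rules out several stronger readings that a reader might infer:

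- *That some 12-month outcomes are settled before enrolment.* The 1-year limit on diagnosis excludes this.
- *That Measures times ART retention from ART start.* This is natural for those who initiate after enrolment, but it is not stated.
- *That points after month 12 cannot be observed.* Clinic records are the gold standard, and the article gives no date when extraction stops. The last survey would miss these points; records might not.
- *That about 94 of 750 have a 6-month point before enrolment (0.25 × 750 × 0.5).* This pools the stated CD4 origin with the inferred ART one and assumes an even spread over 12 months, although selection is from recent register entries.
- *That Measures requires retention at both time points as a composite.* Reporting at each is an equally fair reading.
- *That the sample size assumes an enrolment origin.* It names none.

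What does not stand is the appeal to omitted detail. The article states two different origins for the primary outcome. That is a contradiction, not a gap.

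**Conclusion.** The point holds in this form: the primary outcome has conflicting time origins and does not say consistently whether 12 months alone, or 6 and 12 months, is primary. Under the one alternative origin that is explicit, the effect is small: at most about 19 of 750 register recruits (2.5%). Under an ART-start origin it would be large: up to about 169 more register recruits with outcome time before enrolment, and 394 to 450 first-strategy recruits (281 to 338 under the initial eligibility estimate) with a 12-month point after the intervention year. That spread is itself the reason to settle the wording.

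The counts rest on the planned recruitment mix and expected ART eligibility. The distribution of time from CD4 or ART start to enrolment is not given, so the 25 to 75% range is an assumption. The stated power is not affected.

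**What to change.** In Measures and Table 1, define retention from enrolment for both groups. Make 12 months after enrolment the single primary time point, assessed from clinic records in one stated window around month 12, and make 6 months after enrolment secondary. Replace the timing words in "undergo a repeat CD4 test at 6 months and 12 months after the initial CD4" and "Patients on or initiating ART who remain on treatment 6 and 12 months later" with this wording; deleting them alone would leave the ART row with no time point at all. State the same origin in Sample size estimation, and make sure record extraction runs to the end of the window.

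The cost is wording: visit dates are already extracted weekly or every two weeks, and the surveys already run from baseline. The small downside is that time since the initial CD4 or ART start will vary between participants at the 12-month point; reporting it by arm at baseline would show how much. The change does not remove any selection that comes from recruiting established patients through registers, which is a separate matter.

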## Background

The success of “treatment-as-prevention” trials has ushered in a new era in worldwide HIV prevention efforts [1]. Antiretroviral therapy (ART) suppresses viral replication, effectively forestalling disease progression and reducing the likelihood of viral transmission [2–6]. The landmark HPTN 052 trial among HIV sero-discordant couples found that early ART initiation (when CD4+ cell count is between 350 and 500 cells/μL) can reduce HIV transmission to uninfected partners by 96 % [2]. In countries with a high burden of disease, such as South Africa, where the epidemic remains the world’s largest with an estimated 6.4 million people living with HIV (PLHIV) [7], improving early uptake of and adherence to ART could bring substantial gains in HIV prevention. Modeling suggests that annual HIV testing with the immediate initiation of ART (at any CD4 count) in South Africa could reduce HIV incidence and mortality to less than one case per 1000 people per year by 2016 [8]. Additionally, South Africans residing in communities with greater ART coverage have a lower risk of HIV acquisition [9]. While instituting universal ART coverage will be challenging to implement in resource-constrained settings, important gains can be attained by ensuring that infected individuals are identified early in their HIV disease, enter into care rapidly, and remain in care and adherent to their regimens following the initiation of treatment. Unfortunately, in sub-Saharan Africa, some 40 % of individuals who test positive are not successfully linked to care, and only 50 % of those who are not yet ART-eligible are retained in HIV care [10], leading to a “cascade” of losses at each stage along the care continuum [11].

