### Intervention

Two intervention strategies to increase retention in care (primary outcome), as well as linkage to care, ART adherence, and prevention behaviors (secondary outcomes) will be compared to local standard of care (SOC). The two intervention strategies that participants will receive for the duration of 1 year are as follows: 1) an automated SMS and 2) a peer-navigator (PN) model that also includes some automated SMS.

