Linkage to HIV care	CD4 drawn and results available at clinic within 3 months of testing HIV positive	Intake and Record extraction	Weekly (ART) bi-weekly (pre-ART)
	CD4 result received within 3 months of testing HIV positive	Survey data (self-report)	0 and 6 months
	Patients eligible for ART who initiate treatment within 3 months of CD4 staging	Intake and Record extraction	Weekly (ART)
		Survey data (self-report)	0, 6, and 12 months
Adherence to ART	Proportion taking 90 % and 100 % of pills in the past 30 days	Survey data (self-report)	0, 6, and 12 months
	Breaks in treatment during the previous six months (at least 4 days in a row)	Intake and Record extraction	Weekly (ART)
		Survey data (self-report)	0, 6, and 12 months
	Proportion of days covered (# of dispensed days of medication/# of days between refills)	Intake and Record extraction	Weekly (ART)
Prevention (transmission risk)	Number of unprotected sex acts by partner HIV status	Survey data (self-report)	0, 6, and 12 months

Because the volume and intensity of the intervention might vary, particularly in the PN arm, we will also capture intervention exposure or dosage as a secondary exposure measure. Dose (minutes) of intervention received will be used for per protocol analyses. In the PN arm, this will include recording client data on frequency and duration of in-person meetings and phone communications with the navigator. Delivery and response to SMS messages for both intervention arms will be recorded with a standard duration of exposure (for example, 30 seconds) for each message, including two-way messaging. Any phone or in-person follow-up to SMS messages will be recorded separately. Secondary outcomes include linkage to HIV care, adherence to medications, and transmission risk behavior, as described in Table 1.

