### Analysis

Our preliminary analysis will include presentation of participant demographic characteristics, service usage, acceptability of intervention approaches and self-reported sexual behavior within each of the three study arms using descriptive statistics (one-way and cross-tabular frequency tables and, for continuous variables, measures of central tendency). Measures of variability will account for repeated measures (multiple patients) and consequent correlation of variables (clustering) within each health facility. We will employ multiple imputation (MI) using chained equations to account for missing data. This procedure assumes that incomplete data arise from a missing-at-random (MAR) process, under which missingness is random conditional on observed covariables and observed outcomes rather than a missing-completely-at-random (MCAR) mechanism [43], thus making fewer assumptions about the nature of the missing data. We will conduct sensitivity analysis using weighted MI to evaluate the robustness of the MAR assumption [44].

Our primary analyses will employ an intention-to-treat (ITT) approach. We will employ logistic generalized estimating equations (GEE) to compare patient retention between intervention arms. We will also evaluate secondary outcomes (linkage, adherence and prevention behaviors) using an ITT analysis, as described above. We will employ GEE rather than mixed effects models as this approach allows us to estimate the effect of the intervention at the level of the population, rather than at the level of the individual. As our interventions will be implemented at the level of the health system, it is important to estimate the effect of the intervention at the level it is implemented [45]. Further, previous research has suggested that adjustment for confounding can improve the efficiency of estimates in the context of randomized trials [46]. We will thus conduct sensitivity analyses employing causal inference methods to account for any imbalance in distribution of site- and individual-level co-variables across study clinics. We will employ targeted maximum likelihood estimation [47], which allows estimation of both site- and individual-level co-variables, to minimize bias and improve efficiency of estimates of effect in the context of small sample sizes [48].

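### The ART-linkage measure counts only staged, eligible participants, so its denominator can depend on the intervention and the between-arm comparison is not the promised ITT one

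*Protocol article*

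**What the plan says.** The Measures section sets out two steps of linkage. The first is staging, with the window counted from diagnosis: "The secondary outcome of linkage to care is defined as a patient undergoing CD4 staging or being assessed for ART eligibility within 3 months". The second is linkage to ART, introduced as something the team will also monitor: "whether eligible participants receive ART within 3 months of CD4 staging". Table 1 lists this second step under secondary outcomes in the same terms: "Patients eligible for ART who initiate treatment within 3 months of CD4 staging".

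The other linkage rows of Table 1 record only that a CD4 was drawn with results available, or that the participant received the result. They are not restricted to eligible patients.

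The last paragraph of the Background states the aim as timely linkage to both care and treatment. The Intervention section names linkage among the outcomes that both strategies should improve over standard of care. The Analysis section says: "We will also evaluate secondary outcomes (linkage, adherence and prevention behaviors) using an ITT analysis".

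Under Participant eligibility and recruitment, 75% of participants are to come from a strategy that approaches people receiving a first positive test or collecting a first CD4 result. The other 25% come from HIV care registers.

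**The concern.** A participant who is never staged has no start date for the 3-month clock and, where eligibility rests on a CD4 threshold, no established eligibility. That participant cannot be a failure on the ART-linkage measure and simply leaves its denominator.

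For people enrolled at first diagnosis, staging can come after enrolment, when the intervention may already have acted. Staging is also an outcome that the interventions are meant to raise. An arm that brings more people to staging therefore enlarges its own ART-linkage denominator. If the people added are harder to bring to treatment than those who would have been staged anyway, the arm's percentage falls even though more of its participants start ART.

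The loss at this step is not trivial by the article's own account: "some 40 % of individuals who test positive are not successfully linked to care". At stake is the treatment half of the linkage question, because no other row of Table 1 measures ART start over everyone enrolled and untreated.

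**Working it through.** The plan gives no expected rate or power for this measure, so there is no figure of its own to reproduce. Its only detectable differences (Sample size estimation) concern 12-month retention. The following is an illustration of the mechanism.

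**Inputs**
- Control staging s0 = 0.625 and ART start among eligible a = 0.667. Both are results of a Cape Town study cited in the Background, borrowed here as control rates. The 62.5% is receipt of a CD4 result within 6 months, which differs in event and window from the trial's definition.
- Staging under intervention s1 = 0.80: assumed (range 0.70 to 0.85).
- ART start r among the extra people staged = 0.40 to 0.50: assumed (range 0.30 to 0.667).
- Population: ART-eligible participants not yet staged at enrolment. ART start among those staged in either case is taken as unchanged.

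**Formulas**
- Planned measure: control a; intervention [s0·a + (s1 − s0)·r] / s1. Difference = (s1 − s0)/s1 × (r − a).
- All eligible: control s0·a; intervention s0·a + (s1 − s0)·r. Difference = (s1 − s0) × r.

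**Central case (s1 = 0.80)**
- Control, all eligible: 0.625 × 0.667 = 0.417.
- r = 0.40: numerator 0.417 + 0.175 × 0.40 = 0.487; planned measure 0.487/0.80 = 60.9%.
- r = 0.50: numerator 0.417 + 0.175 × 0.50 = 0.504; planned measure 0.504/0.80 = 63.0%.

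| r | Planned measure, intervention v control | Difference | All eligible, intervention v control | Difference |
|---|---|---|---|---|
| 0.30 | 58.7% v 66.7% | −8.0 | 46.9% v 41.7% | +5.2 |
| 0.40 | 60.9% v 66.7% | −5.8 | 48.7% v 41.7% | +7.0 |
| 0.50 | 63.0% v 66.7% | −3.7 | 50.4% v 41.7% | +8.8 (0.175 × 0.50 = 0.0875) |
| 0.667 | 66.7% v 66.7% | 0 | 53.4% v 41.7% | +11.7 |

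The formulas show when the signs part: whenever staging rises and r lies above zero but below a. At r = a the planned measure shows nothing and the gain is hidden.

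**Other staging rates (r = 0.50).** With s1 = 0.70, the planned difference is 0.075/0.70 × (−0.167) = −1.8 points and the all-eligible difference is 0.075 × 0.50 = +3.8. With s1 = 0.85, they are 0.225/0.85 × (−0.167) = −4.4 and 0.225 × 0.50 = +11.3.

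**Participants already staged at enrolment (s1 = 0.80, r = 0.50).** Let a share w be already staged and start ART at 0.667 in both arms. The document gives no value for w. The planned difference becomes (1 − w)(0.175)/[w + (1 − w)(0.80)] × (−0.167), and the all-eligible difference becomes (1 − w)(0.0875).

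| w | Planned measure | All eligible |
|---|---|---|
| 0.25 | −2.6 | +6.6 |
| 0.50 | −1.6 | +4.4 |
| 0.75 | −0.8 | +2.2 |

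**The case against.** **Failure to be staged is already counted.** A reader might infer that people never staged drop out of the trial's linkage results altogether. They do not: they fail the staging outcome, which is reported alongside, so a shift in denominators would be visible. This stands, and it is the main reason to rate the point as minor. It does not supply the missing quantity, since no row gives ART start over all untreated participants.

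**Staging may leave little room for change.** The record-based row needs a CD4 drawn and the result available at the clinic; the patient need not return for it. Some participants are recruited when collecting a first result, and the register recruits (25%) are expected to be ART-qualified in upwards of 90% of cases. If blood is usually drawn at or near diagnosis, few denominators can move. This also stands. The article does not state the timing of the draw, and the table for w shows the distortion shrinking accordingly.

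**The sign change rests on assumptions.** A reader might infer that the measure will show harm, or that 62.5% and 66.7% are the trial's own control assumptions. The documents support neither. The rates come from a cited study, the only control rate the protocol assumes is 50% retention, and the 80% and 40-50% are assumed here. Distortions of a few points are also small beside the 17 to 23 points for which the trial is powered on retention, so a statistically significant reversal is unlikely. A missed or muted benefit is the more realistic cost.

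**Imputation could cover undetermined eligibility.** The article does say "We will employ multiple imputation (MI) using chained equations to account for missing data", but it does not extend this to people never staged. Not being staged is also a care outcome rather than a missing value.

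**Step-wise reporting is normal for a care cascade.** Agreed. It serves as description, but it is not a randomised comparison.

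**Conclusion.** The point holds for participants whose staging follows enrolment. For them the ART-linkage denominator can be shaped by the intervention, so the arm comparison on this measure is not the ITT comparison that the Analysis section promises. The document states both the restriction to eligible patients and the time origin, twice, so this is not a detail left to an analysis plan.

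In the illustration, the planned measure is 3.7 to 5.8 points lower under intervention while the proportion of all eligible, initially unstaged participants starting ART is 7.0 to 8.8 points higher. The direction of the distortion depends on the extra people staged starting ART less often than the others. Its size depends on how far the interventions raise staging and on how many participants are already staged at enrolment. None of these is given in the document. A reversal is possible, not established.

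Severity is minor: one component of a secondary outcome, with the staging outcome reported beside it.

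**What to change.** In Measures and Table 1, make the between-arm ITT comparison for ART linkage the proportion with documented ART start within a fixed time from enrolment (or diagnosis) among all participants not on ART at enrolment. Include those already staged but untreated at enrolment, and count the never-staged as not started. Enrolment is the simpler origin: participants may be diagnosed up to a year earlier, so a short window from diagnosis could have closed before they enrol. Report the proportion known to be ineligible by arm beside it, and keep the percentage among staged, eligible patients as a descriptive cascade step.

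The cost is wording only. Record extraction already captures visits, medications and CD4 results, and nothing in clinical management changes. The downside is lower absolute percentages and some dilution from participants who are not ART-eligible. The article expects 70-80% of those newly diagnosed after January 2015 to qualify. If ineligible participants contribute no starts, the illustrative gain of 7.0 to 8.8 points would become 0.70 × 7.0 = 4.9 to 0.80 × 8.75 = 7.0 points among those unstaged at enrolment.
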